##### Phase 2: live patient evaluation

Phase 2 will entail a live patient evaluation study of the IDDEAS CDSS model for the diagnosis and treatment of ADHD among children and adolescents in which seven standardized patient-encounter videos will be assessed with and without the use of the IDDEAS system. The aim of this phase of the study is to determine whether IDDEAS in its entirety can: meet the desired requirements; can yield an output that meets specifications with acceptable capability.

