While CDSS implementation in general medicine has been found to be advantageous for the quality of services [30, 31], there is limited evidence on the use of CDSSs for CAMHS [32]. One reason for such limited research is the lack of accessibility to psychiatric data, especially those pertaining to children and adolescents. From the established studies on CDSSs in CAMHS however, most have identified various limitations, including a lack of integration with the EHR, limited predictive models for diagnosis, and inadequate inclusion of multiple disorders [32]. Norway is in a unique position to develop and implement a CDSS for CAMHS because it can potentially avoid previously identified limitations. Over the past decade, the Norwegian National Association of Child and Adolescent Mental Health (N-BUP), has collected extensive data on CAMHS and compiled unique and rich datasets, based on advanced, multidisciplinary EHRs. However, these datasets have yet to be optimally utilized for subsequent care, as maintaining access requires ethical clearance and completion of a local data protection impact assessment (DPIA) and risk assessment to ensure privacy and confidentiality will not be breached.

This paper presents the study design and protocol for the evaluation of the first CDSS for CAMHS in Norway, the Individualized Digital Decision Assist System (IDDEAS). IDDEAS is an innovative research project, contributing to the HELSEVEL Programme (Programme on Health, Care and Welfare Services Research) and funded by the Norwegian Research Council (NFR). The overall aim of IDDEAS is to improve patient care by providing practitioners with real-time, data-driven and evidence-based guidance that ensures earlier and more precise decision-making, avoids misdiagnosis and reduces inefficiency in patient care practices. The principal benefit of the study is to examine the provision of decision support for clinicians in real-time during clinical sessions and improvement of clinical care.

The objectives of the IDDEAS project include:

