#### Procedure

The evaluation of the CDSS model initially will entail assessments of how child and adolescent psychologists and psychiatrists perceive the usability, acceptability, validity, and relevance of the CDSS model for use in their clinical practice. The evaluation of the CDSS model will take place in two phases, as follows: Phase 1. Vignette-Based Evaluation and Phase 2. Live Patient Evaluation. Both phases of the CDSS evaluation will occur in randomly selected CAMHS clinics. The incremental evaluation phases will take place within the trial period of August 2020–2023. Using a pre-post design, for both phases of the evaluation, participants will compare the provision of clinical care with use of the CDSS, to the daily clinical practice, as the control. Prior to participation in the evaluation written consent will be obtained from all participants by the project leader. Participants will be informed their participation is voluntary and they can withdraw from the study at any time without penalty.

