##### Phase 1: vignette-based evaluation

After completion of informed consent procedures, including assessments of conflicts of interest, clinicians will be asked to complete a brief demographic questionnaire. They will then be provided the educational manual on how to navigate the IDDEAS system. Clinicians will then be asked to critically appraise ten previously validated clinical case vignettes (i.e., fictional patient cases that have been “referred” for assessment of ADHD). Clinicians will first appraise five of the cases without the use of the system and five using the CDSS. The cases will be randomly allocated by the PhD student with the project and verified by the project leader. The allocation sequence will be computer generated.

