#### Data collection

##### Qualitative methods

All participants will be surveyed using both qualitative and quantitative methods. In the vignette-based evaluation, all participants will be asked to complete a “cognitive- walkthrough” in which they will think-aloud through the entire process of critically appraising each clinical vignette case. In the live patient evaluation, the same procedure will be conducted to evaluate clinical care with the CDSS, based on seven standard patient encounter videos. All participants will be queried with a semi-structured interview in order to gain understanding of the participants’ overall experience, challenges encountered, strengths, and any other aspects of the system requiring adjustment. The semi-structure interviews will be held directly after the completion of the case vignettes. For both phases of the evaluation, the cognitive-walkthrough and semi-structured interview will be audio recorded and transcribed. Transcripts will be transferred to NViVo 10 software for coding and data analysis [33, 34].

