#### Outcomes

The primary outcome of the study will be the clinical utility of the IDDEAS CDSS for diagnosis and treatment of child and adolescent mental health disorders. The primary outcome will be measured by reviewing participants’ clinical diagnosis and treatment plans as a measure of sensitivity and specificity when using the CDSS compared to when not using the CDSS, upon completion of both phases of the evaluation.

The secondary outcomes of the study will be subjective measures. The three secondary outcome measures are perceived clinical usability, perceived clinical relevance and validity, as well as perceived appropriateness of the IDDEAS CDSS. The perceived clinical usability of the CDSS will be measured using the system usability scale (SUS) [33, 39, 40]. The perceived appropriateness of the CDSS will be measured using the user-engagement scale (UES) [41–43]. The perceived clinical relevance and validity of the system’s user-interface will be measured using the content validity index (CVI) [44].

All outcomes will be measured directly following both phases of the evaluation of the IDDEAS CDSS (i.e., within 24 h).

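### Phase 2 appears to have the same seven recorded videos read first without and then with IDDEAS; if so, any second-look effect cannot be separated from the CDSS effect, and the live-patient label does not fit the material

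*Protocol article*

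**What the plan says.** The section on Phase 2 opens with "Phase 2 will entail a live patient evaluation study of the IDDEAS CDSS model" and then defines the material: "seven standardized patient-encounter videos will be assessed with and without the use of the IDDEAS system". The data collection section on qualitative methods again bases the assessment with the system on the whole set: "to evaluate clinical care with the CDSS, based on seven standard patient encounter videos".

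The Procedure section fixes the order of conditions: "Using a pre-post design, for both phases of the evaluation, participants will compare the provision of clinical care with use of the CDSS", with daily clinical practice as the control.

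Phase 1 is arranged differently. It has ten vignettes, and "Clinicians will first appraise five of the cases without the use of the system and five using the CDSS", with computer-generated allocation of cases. Nothing equivalent is stated for Phase 2.

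The quantitative analysis is a mixed logistic model for correct diagnosis, with decision support and patient status (ADHD or not) as fixed effects. Under Outcomes, sensitivity and specificity with and without the CDSS are compared after both phases, so Phase 2 feeds the primary outcome. That outcome is worded as the "clinical utility of the IDDEAS CDSS for diagnosis and treatment of child and adolescent mental health disorders". The Background gives the principal benefit of the study as to "examine the provision of decision support for clinicians in real-time during clinical sessions and improvement of clinical care".

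**The concern.** Two things look wrong.

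The first is the comparison itself. If a clinician judges a video unaided and later judges the same video with the CDSS, the second judgement has both the CDSS and a second look behind it. Recall of the case, more time to think and a chance to reconsider all coincide with CDSS use. The contrast that is meant to show diagnostic benefit would then measure the sum of these effects, and it enters the primary outcome.

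The second is what the phase can support. Recorded encounters are not live patients, and the cases are assessed for ADHD. The label and the outcome wording would allow a conclusion about real-time care, and about child and adolescent disorders in general, that neither phase examines.

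**Working it through.** **Step 1: are the same videos read under both conditions?**

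| Feature | Phase 1 | Phase 2 |
|---|---|---|
| Material | 10 vignettes | 7 recorded videos |
| Division between conditions | 5 without, 5 with | none stated; the set is assessed with and without |
| Allocation of cases | computer generated | none stated |
| Order | unaided first | pre-post, so unaided first |

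The plain reading of Phase 2 is one set of seven, read under both conditions. The pre-post term alone does not establish this, because Phase 1 carries the same term and uses different cases per condition. It establishes only the order.

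**Step 2: can the analysis separate the effects?** Let *d* be the effect of decision support and *r* the effect of a second reading. If every unaided reading is first and every aided reading is second, the aided-minus-unaided contrast estimates *d* + *r*. An order term would take the same value as the decision-support term in every Phase 2 reading, so adding one would not help. The effects can be separated only by changing the design.

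**Step 3: how large could it be?** The documents give no figure for *r*, so this is an illustration.

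From the plan:
- 30 clinicians.
- Unaided specificity 0.50, planned to rise to 0.80, a difference of 0.30.

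Assumed:
- 3 or 4 of the seven videos are non-ADHD.
- The CDSS has no effect.
- On second look, a share *c* of wrong answers is corrected and a share *s* of correct answers is spoiled.
- Readings are independent.
- The test is an exact two-sided McNemar test at 0.05, counted when it favours the CDSS.

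The apparent gain in specificity is (1 − 0.50) × *c* − 0.50 × *s*. The number of paired readings is 30 × 3 = 90 or 30 × 4 = 120.

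| *c* corrected | *s* spoiled | Apparent gain | False benefit, 3 videos | False benefit, 4 videos |
|---|---|---|---|---|
| 10% | 10% | 0.050 − 0.050 = 0 | 1% | 1% |
| 10% | 5% | 0.050 − 0.025 = 0.025 | 6% | 9% |
| 20% | 10% | 0.100 − 0.050 = 0.050 | 16% | 22% |
| 20% | 5% | 0.100 − 0.025 = 0.075 | 42% | 58% |

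A gain of 0.075 is 0.075 / 0.30 = one quarter of the planned effect. The table shows that the result turns on the net second-look gain. With changes equal in both directions there is almost no false benefit.

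**Step 4: the plan's own figure.** The sample size of 30 can be approached from the stated effect size of 1.0: 2 × (1.96 + 0.84)² / 1.0² ≈ 15.7, so 16 per group and 32 in total, close to 30. The present point does not depend on this figure.

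**Step 5: label and scope.** Phase 2 is called a live patient evaluation, but its only stated material is recorded video. Both phases concern assessment of ADHD, and patient status in the model is ADHD or non-ADHD. The primary outcome wording carries neither limit.

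**The case against.** The strongest reply is that the article never says outright that each clinician views every video twice. The same words could describe a set divided across conditions or clinicians. An odd number is no obstacle, since seven can be split three and four. A condensed article may also leave the viewing schedule, or a washout, to the full protocol. This stands as a reason to state the confounding conditionally. It does not remove the point: the text names one set under both conditions and gives no split, although it gives one for Phase 1. A washout would weaken recall but leave order aligned with condition.

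A reader might infer that the bias must favour the CDSS. The documents do not support that. A second look plausibly helps, but anchoring on the first answer or fatigue could push the other way. Nor do they say that clinicians keep notes or carry forward a think-aloud from the unaided reading. The Phase 2 think-aloud is described only for care with the CDSS.

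The error rates in the illustration rest on assumed correction and spoiling rates, an assumed case mix and a simpler test than the planned mixed model. They show what is possible and do not estimate what will happen.

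On scope, the article does say that ADHD is the first clinical model and discloses the videos in the same sentence as the label. A careful reader would not be misled about the material. The outcome wording still goes beyond it.

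**Conclusion.** The point holds in conditional form. If each clinician reads each of the seven videos without and then with IDDEAS, which is the plain reading, a second-look effect is fully confounded with the CDSS effect in the Phase 2 part of the primary comparison, and the planned model cannot separate them.

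The sign is plausibly in favour of the CDSS but not established, and the size is unknown. With no CDSS effect and the assumptions above, false benefit ranges from about 1% of trials (10% corrected, 10% spoiled) through 6-9% (10%, 5%) to 42-58% (20%, 5%). It would be wrong to take the upper figures as an expected error rate.

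Separately, and whatever the viewing schedule, the live-patient label and the general outcome wording claim more than recorded ADHD assessments can support, because no live patient and no other target disorder is evaluated.

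**What to change.** - **Viewing schedule.** Have each clinician see each video once. Assign a random 3 or 4 of the seven to the CDSS for 15 clinicians and give the other 15 the complementary split, balanced by ADHD status where the case mix allows. Each video is then read 15 times in each condition, so differences in difficulty between videos do not favour either one. If the full protocol already divides the videos, the article should say so.
- **Order.** The split removes repeat viewing even if the unaided block stays first. A general practice effect then remains and should be stated as a limitation. Randomising the order would address it, but clinicians who start with the CDSS could carry its prompts into their unaided cases. That is a trade-off for the sponsor and need not be required.
- **Wording.** Rename Phase 2 a standardised video evaluation. Word the primary outcome and the conclusion as diagnostic and treatment-plan accuracy for ADHD in vignettes and recorded encounters.

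Cost: Phase 2 readings fall from 30 × 7 × 2 = 420 to 30 × 7 = 210, and the pairing of the same video within a clinician is lost, so precision drops. Viewing time is halved. The rest is a change of text.

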#### Data collection

##### Qualitative methods

All participants will be surveyed using both qualitative and quantitative methods. In the vignette-based evaluation, all participants will be asked to complete a “cognitive- walkthrough” in which they will think-aloud through the entire process of critically appraising each clinical vignette case. In the live patient evaluation, the same procedure will be conducted to evaluate clinical care with the CDSS, based on seven standard patient encounter videos. All participants will be queried with a semi-structured interview in order to gain understanding of the participants’ overall experience, challenges encountered, strengths, and any other aspects of the system requiring adjustment. The semi-structure interviews will be held directly after the completion of the case vignettes. For both phases of the evaluation, the cognitive-walkthrough and semi-structured interview will be audio recorded and transcribed. Transcripts will be transferred to NViVo 10 software for coding and data analysis [33, 34].

##### Quantitative methods

All quantitative measurements will be translated from English to Norwegian as needed and compiled into an assessment package in accordance with the WHO’s guideline “Process of Translation and Adaptation of Instruments” (see Table 1) [35]. Data will also be collected on the sensitivity, specificity, and relevance of the IDDEAS system. Data will be collected on standardized score sheets, transferred to a Microsoft Excel spreadsheet, and retained/stored in a database system serving as a scalable informatics framework (i.e., Informatics for Integrating Biology & the Bedside (i2b2)) for subsequent analysis. The database system will provide an ontology-based flexibility that enables aggregation of multiple datasets, as well as easy extraction of individual clinical cases. All participants’ demographic information will also be anonymized with a randomly assigned unique study ID, aggregated and encrypted prior to transfer to a secure data repository for storage. Access to participants’ demographic information and study IDs will only be available to the IDDEAS project leader and the PhD student affiliated with the project. Datasets will be stored in a secure data repository at the Regional Center for Child and Youth Mental Health and Child Welfare (RKBU), Department of Mental Health, Norwegian University of Science and Technology (NTNU).

**Table 1 Tab1:** Quantitative Assessment Measurements

Full Name	Abbreviation	About	Measure
System Usability Scale	SUS	To establish each participant’s individual rating score of usability aspects (e.g. the ability of users to complete tasks, level of resources/effort needs for task completion, and user’s subjective reaction to the system.)	Perceived Usability
User-Engagement Scale	UES	Measure user engagement with the system, including: appropriateness for clinical session, focused attention, aesthetics appeal, and felt involvement	Appropriateness
Content Validity Index	CVI	To capture inter-rater agreement on the relevance and appropriateness of each proposed item.	Relevance

#### Data analysis

##### Qualitative methods

For both phases of the evaluation, the semi-structured interviews and the “cognitive- walkthrough” recordings, will both be analyzed using thematic (i.e., Grounded Theory) and content analysis. The thematic analysis will identify patterns within the participants’ transcribed response to identify attributes of the overall appropriateness, including: challenges experienced assessing the cases, limitations in the interactive component of the system, strengths of the system’s design, and potential additions to the system’s design in order to improve the experience. Content analysis will be used to assess the frequency of items and prompts used during the interviews [33, 36, 37].

##### Quantitative methods

The Likert scale items will be assessed based on inter-rater reliability in accordance with pre-specified and previously validated criteria. The usability, content validity, and user engagement data will be compiled and analyzed with statistical analysis software (SPSS software platform) to determine whether the criteria are met for each measurement (i.e., SUS ≥ 70; UES ≥ 70; CVI > 0.80) [38]. The criteria will be analyzed by computing the average of the rating scores proposed by participants for each Likert item and finding the degree of inter-rater agreement on the IDDEAS system attributes (i.e., prompt/alert provided in system user-interface).

The sensitivity, specificity, and relevance of the IDDEAS system for ADHD diagnosis and treatment will also be assessed based on overall percentage of agreement among participants on appropriate diagnosis, as well as the proposed biopsychosocial treatment plan. A mixed model logistic regression will be used with correct diagnosis as the dependent variable, decision support (yes or no) and patient status (ADHD or non-ADHD) as fixed effects.

#### IDDEAS CDSS system modification and refinement

Between the two phases of the IDDEAS evaluation study, adjustments to the measurement tools and the system will be made. Based on the results of the vignette-based evaluation, prior to the live patient evaluation, adjustments to the questionnaires, the CDSS content provided for practitioners, and the overall design of the user-interface will be adjusted as necessary.

#### Outcomes

The primary outcome of the study will be the clinical utility of the IDDEAS CDSS for diagnosis and treatment of child and adolescent mental health disorders. The primary outcome will be measured by reviewing participants’ clinical diagnosis and treatment plans as a measure of sensitivity and specificity when using the CDSS compared to when not using the CDSS, upon completion of both phases of the evaluation.

The secondary outcomes of the study will be subjective measures. The three secondary outcome measures are perceived clinical usability, perceived clinical relevance and validity, as well as perceived appropriateness of the IDDEAS CDSS. The perceived clinical usability of the CDSS will be measured using the system usability scale (SUS) [33, 39, 40]. The perceived appropriateness of the CDSS will be measured using the user-engagement scale (UES) [41–43]. The perceived clinical relevance and validity of the system’s user-interface will be measured using the content validity index (CVI) [44].

All outcomes will be measured directly following both phases of the evaluation of the IDDEAS CDSS (i.e., within 24 h).

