#### Sample size

The sample size was calculated based on the optimal power value in order to ensure the size of the sample is appropriate for this study. There is the assumption that the effect of decision support is to increase specificity from 0.50 to 0.80 and only moderately change sensitivity. With the assumption that the effect of decision support is to increase specificity from 0.50 to 0.80 and only moderately change sensitivity, the sample size (*n* = 30) can be calculated with an effect size of at least 1.0 and desired power value of .80 (80%); the assumption of the specificity increase, to detect the statistical significance (*p* < 0.05) on a dichotomous variable with 80% power, the number of subjects required is 30.

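### The Outcomes, Sample size and Data analysis sections point to different primary comparisons, and none says which one decides whether IDDEAS has clinical utility

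*Protocol article*

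**What the plan says.** Three sections of the protocol article (Stage 3) bear on the primary comparison.

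- **Outcomes.** Clinical utility is primary and is assessed through "reviewing participants’ clinical diagnosis and treatment plans as a measure of sensitivity and specificity when using the CDSS compared to when not using the CDSS". Timing covers both phases: "All outcomes will be measured directly following both phases of the evaluation of the IDDEAS CDSS". The section does not say whether one or both measures must improve, how the treatment plan counts, or whether the phases are combined.
- **Sample size.** The assumption is that "the effect of decision support is to increase specificity from 0.50 to 0.80 and only moderately change sensitivity". The calculation is made "to detect the statistical significance (*p* < 0.05) on a dichotomous variable with 80% power", and "the number of subjects required is 30". No phase is named. This is the only significance level in the article, and it is attached to one contrast.
- **Data analysis, Quantitative methods.** "A mixed model logistic regression will be used with correct diagnosis as the dependent variable, decision support (yes or no) and patient status". The last two terms are its fixed effects. No interaction is named. Treatment plans are assessed by percentage agreement, with no test stated.

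A fourth section, on system modification and refinement, says that both the measurement tools and the system are adjusted between the phases in the light of Phase 1.

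**The concern.** Each section is reasonable alone, but together they give the primary question three targets: a pair of accuracy measures for two kinds of judgement, specificity only, and overall correctness of diagnosis. The results can differ in sign or significance, and the article would then not say whether utility had been shown.

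Two things are at stake. The first is the conclusion itself: the sized contrast may succeed while the modelled one does not, or the reverse. The second is error control: if the deciding contrast is chosen after the results are known, the 0.05 in the sample-size paragraph no longer describes the chance of a false claim. The phases add to both problems, because vignettes and videos are different material and the system under test is not the same version.

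**Working it through.** **1. The plan's own figure.** Inputs from the Sample size section: 0.50 to 0.80, effect size 1.0, power 0.80, p < 0.05, sidedness not stated.

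- Two means, two-sided: n = 2(1.960 + 0.842)²/1.0² = 15.7, so 16 per group and 32 in total.
- Two proportions, one-sided: n = [1.645√(2 × 0.65 × 0.35) + 0.842√(0.25 + 0.16)]²/0.30² = 30.2, so 31 per condition. The arcsine version gives 29.9.
- Two proportions, two-sided: 39 per condition, which does not match.

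The stated 30 is therefore recovered to within 2, by either of the first two routes, as the size for a **single** contrast at 0.05.

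**2. What the named model estimates.** Among non-ADHD cases the probability of a correct diagnosis is the specificity; among ADHD cases it is the sensitivity. With main effects only, the decision-support coefficient is one common shift in log-odds for both. A separate specificity contrast needs a decision-support by patient-status interaction.

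**3. Can the targets disagree?** Specificity moves as the article assumes. The article gives no figures for sensitivity, so a fall from 0.80 to 0.65 and an equal case mix are assumed here for illustration.

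| Quantity | Without CDSS | With CDSS | Change in log-odds |
|---|---|---|---|
| Specificity | 0.50 | 0.80 | ln(4) − ln(1) = +1.39 |
| Sensitivity (assumed) | 0.80 | 0.65 | ln(0.65/0.35) − ln(4) = −0.77 |
| Overall correctness | (0.50 + 0.80)/2 = 0.65 | (0.80 + 0.65)/2 = 0.725 | |

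The simple average of the two log-odds changes is (1.39 − 0.77)/2 = +0.31. The sized contrast shows the full planned gain of 0.30, while overall correctness gains 0.075.

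**4. False-positive rate, conditional on the decision rule.** For k independent tests at 0.05 the chance of at least one false positive is 1 − 0.95^k: 0.0975 for k = 2 and 0.185 for k = 4. For correlated tests, equally correlated normal statistics were simulated (400,000 draws, each tested at |z| > 1.96).

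| Rule | Correlation 0 | 0.5 | 0.9 |
|---|---|---|---|
| Any of 2 (sensitivity, specificity) | 0.098 | 0.091 | 0.070 |
| Any of 4 (the same, in each phase) | 0.186 | 0.155 | 0.094 |
| One coefficient decides | 0.05 | 0.05 | 0.05 |
| Both measures must succeed | ≤ 0.05 | ≤ 0.05 | ≤ 0.05 |

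A second run with 1,000,000 draws gave 0.090 and 0.156 at correlation 0.5. Counting only false claims of benefit (one tail, nominal 0.025), the re-run rates at 0.5 were 0.046 and 0.078. The correlations are assumptions; the article gives nothing from which to estimate them.

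**The case against.** The strongest reply is that the article contains no rule allowing any single significant result to count. Sensitivity and specificity are joined by *and*, which may mean that both must improve; the error rate is then at most 0.05. The one named model could equally be the single deciding test, with no inflation. The article is also condensed, so a hierarchy or alpha split may sit in the full protocol or analysis plan, and its absence here is not a fault. All of that stands.

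A reader might go further and infer that a false claim of utility is two to four times as likely as stated, or that eight contrasts (two measures, two judgements, two phases) are each tested at an uncorrected 0.05. The documents do not support this. The 0.05 appears once, for one contrast, in a sample-size calculation. Treatment plans have no stated test, which removes half of the supposed eight. Separate tests by phase are not stated either. The multiplier depends wholly on the rule and correlation assumed, and it starts at 1.

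What the reply does not remove is the disagreement between sections. Taking the named model as decisive leaves the sample size resting on a contrast that the model does not estimate. Requiring both measures leaves a trial sized for only one of them. Further detail elsewhere would not make the published sections agree.

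**Conclusion.** The point holds as a conflict over which comparison decides, and it should be resolved before analysis. The sample size is for one specificity contrast, the model gives one overall effect, and the primary outcome names more than either.

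The illustration (a specificity gain of 0.30 beside an overall gain of 0.075) rests on the assumed sensitivity figures and equal case mix. It shows that the answers can diverge, not that they will. Inflation of the error rate is conditional: none if one coefficient decides or both measures must succeed; about 0.09 (two contrasts) or 0.16 (four) at correlation 0.5 if any one may be claimed; and 0.07 for two at correlation 0.9. It is not an established property of the plan.

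**What to change.** - **Outcomes:** name one deciding contrast and one phase, or state how the phases are pooled. Specificity of the ADHD diagnosis with versus without the CDSS is a natural choice, because the sample size is built on it. State the two-sided level.
- **Data analysis:** add the decision-support by patient-status interaction, and take the specificity contrast from the non-ADHD cases in that model.
- **Sample size:** state which phase the n = 30 refers to. The article does not show that 80% power holds for one phase alone, so this needs confirming.
- **Remaining comparisons:** test specificity in the other phase and then sensitivity in fixed sequence at the same level, stopping at the first failure. Always report sensitivity with its confidence interval beside specificity, so that a gain in one is not read without a loss in the other. Label treatment-plan agreement and overall correctness as secondary.

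The cost is revised text and one extra model term; the naming and ordering add no clinicians or cases. A fixed sequence keeps the full 0.05 for the first step. An even split over two contrasts would take a nominal 80% power to Φ(1.960 + 0.842 − 2.241) = 0.71. The downsides are that results after a failed step are not confirmatory, and that the treatment plan leaves the deciding test, which narrows the primary outcome as now worded.
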